### Recruitment

Participants will be recruited through flyers distributed by the research team that briefly describe the study and how to contact research staff for more information. Research staff will be present at the study site on a weekly basis to provide information in person. Interested participants who make contact with the research staff will be offered a brief eligibility screening. Participants who are eligible will be asked to provide their informed consent for enrollment.

Recruitment activities are planned to take place over 24 months. Administrative staff at the study site reported that there are about 30 young adults meeting eligibility criteria enrolled in the clinic services at any given time, with about 4 new enrollments per month. We estimate a 10% refusal rate based on the low rates of refusal in the previous Just Do You trial, which will allow us to recruit the sample over 24 months. To enhance tracking and retention for follow-up assessments, we will collect extensive contact information for all participants, which includes contact information for up to 3 individuals who will be able to locate them, and use reminder calls or texts for assessment appointments.

### Randomization

Upon enrollment in the study, participants will be assigned to an experimental condition using a randomization plan programmed into a database on the REDCap (Research Electronic Data Capture) platform [81]. The program will assign participants using block randomization to maximize balance across conditions (ie, random assignment to 1 of 8 conditions per block). Condition assignments will be unblinded.

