### Study Setting

Young adult participants will be recruited from an outpatient psychiatric rehabilitation program (the study site) in the eastern United States that serves a community of primarily adult Black and Hispanic or Latine individuals. Mental health services offered by the study site include therapeutic and skills-based group treatment, individual counseling, medication support, and resource coordination for transportation, housing, employment, and other recovery supports.

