### Assessment Procedures

Assessments of engagement will occur at baseline, posttest (after intervention completion), and 3-month follow-up. At each assessment, participants will report on involvement in their treatment, and their perceptions of stigma, benefits, trust and rapport with providers, hopefulness, and the difficulty associated with treatment engagement. In-depth acceptability interviews will be conducted at posttest with 40 participants purposively sampled from each experimental condition. Acceptability interviews will be focused on experiences with intervention components, aspects of implementation, and any factors that promoted or impeded intervention adherence. Each assessment is expected to last for 1 hour.

Screening, consent, and assessment interviews with participants will be administered by the principal investigator or another trained member of the research team and will take place in person at the study site or via encrypted videoconferencing. All staff involved in data collection will be trained on the assessments by the principal investigator, and all research staff will complete training on informed consent, good clinical practices, and all safety and reporting protocols as certified by New York University’s institutional review board (IRB).

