### Study Timeline

The study will take place over 4-5 months for each participant, and the total study duration is expected to last 2.5 years. Consenting participants will be enrolled, randomized, and administered a baseline assessment on the first day. They will be scheduled to receive the Just Do You core component within 1 week of completing the baseline. They will receive each subsequent component within 1 week of the previous component based on their experimental condition (Figure 2). After completing the intervention, participants will be administered the posttest assessment, which includes the study outcomes and acceptability measures. Participants will be administered the final assessment 3 months after the baseline, and the research staff will receive a report from the study site documenting each date a treatment service was received by the participant over the study period.

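### As described, the randomization blocks are predictable near their end to unblinded enrolling staff, and the REDCap list does not prevent this

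*Protocol article*

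**What the plan says.** All of the following is in the protocol article.

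- **Randomization.** The sequence is applied "using a randomization plan programmed into a database on the REDCap (Research Electronic Data Capture) platform". On blocking: "The program will assign participants using block randomization to maximize balance across conditions", explained in parentheses as "random assignment to 1 of 8 conditions per block". The section ends: "Condition assignments will be unblinded".
- **Pilot Trial Design, Table 1.** There are 8 conditions with 10 participants each, 80 in all. Each component is present in four conditions and absent in four, so each main effect compares 40 with 40.
- **Study Setting.** There is one site: "an outpatient psychiatric rehabilitation program (the study site) in the eastern United States".
- **Assessment Procedures.** "Screening, consent, and assessment interviews with participants will be administered by the principal investigator or another trained member of the research team".
- **Intervention and Process Evaluation.** Sessions are delivered by a clinician and a peer specialist who work for the site. The principal investigator meets them every week.
- **Study Timeline.** "Consenting participants will be enrolled, randomized, and administered a baseline assessment on the first day".

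The article does not give the block size as a number, and does not say whether it varies or who is kept from the running list of assignments.

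**The concern.** If each block holds every condition once, each open assignment removes one condition from those still to come. Someone who has followed a block knows what is left, and the eighth place is known before anyone is approached for it. A sequence held in REDCap hides the next cell but not what past assignments reveal. Consent before randomization protects only when the next cell cannot be foreseen.

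The enrolling side can know past assignments. The principal investigator may screen and consent, and also supervises the interventionists weekly. At the feasibility benchmark of 3 participants a month, a block of 8 lasts 8/3 = 2.7 months, so keeping a tally takes little effort.

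The timing of a given client's enrolment could then be influenced, even unintentionally. Conditions run from 1 to 5 weekly sessions, and the outcomes are self-reported engagement, service contacts and component completion. All of these depend on how engaged a client already is. If more engaged clients tended to enter when longer conditions were due, the component contrasts on engagement, contacts and adherence would be distorted.

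**Working it through.** The article gives no figure for predictability, so there is none to reproduce. Its 79% power does not depend on the blocking.

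**Inputs**

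- 8 conditions, 10 each, 80 in total (Table 1).
- Each component present in 4 of the 8 conditions (Table 1).
- Block size 8, one place per condition. This is inferred from the parenthesis in Randomization; it fits Table 1, since 80/8 = 10 whole blocks.
- Assumption: the person guessing knows every past assignment and where each block began. The guess rates below are therefore upper limits.

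**Blocks of 8: exact condition**

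- Certain only at the last place: 1/8 = 12.5%, or 10 of 80 allocations.
- At most two conditions left at the last two places: 2/8 = 25%.
- Best guess right: with k places left the chance is 1/k, so the average is (1 + 1/2 + … + 1/8)/8 = 2.718/8 = 0.340. Simple randomization gives 1/8 = 0.125.

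**Blocks of 8: level of one given component (4 with, 4 without)**

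- The level is certain once all remaining places share it, that is, over the final run of the block. The expected length of that run is 4/5 + 4/5 = 1.6 places, so 1.6/8 = 20%, or 16 of 80 allocations.
- Best guess right: [4 + (2^8/C(8,4) − 1)/2]/8 = [4 + (256/70 − 1)/2]/8 = 5.329/8 = 0.666. Simple randomization gives 0.5.
- By simulation, at least one of the three components is certain for 29.5% of allocations.

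**Other block sizes, for comparison**

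- Fixed 16, condition certain: the final run has expected length 1 + 1/15 = 1.067, so 1.067/16 = 6.7%.
- Fixed 16, given component certain: (8/9 + 8/9)/16 = 11.1%.
- Mix of 8 and 16, drawn with equal chance, current size hidden but block starts known: only blocks of 16 yield certainty, after their eighth place. Two such blocks use 24 places on average. The condition is certain for 1.067/24 = 4.4% and a given component for (16/9)/24 = 7.4%.

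| Scheme | Condition certain | Component certain | Best guess, condition | Best guess, component |
|---|---|---|---|---|
| Blocks of 8 | 12.5% | 20.0% | 34.0% | 66.6% |
| Blocks of 16 | 6.7% | 11.1% | 29.6% | 62.8% |
| Mix of 8 and 16, size hidden | 4.4% | 7.4% | 31.0% | not computed |
| Simple randomization | 0 | 0 | 12.5% | 50% |

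The condition guess rates for blocks of 16 and for the mix come from simulation. Mixing sizes mainly removes certainty; the best-guess rates fall only modestly.

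**The case against.** **The block size is not stated.** This is correct, and a journal article may leave block size and custody of the list to the full protocol. But the article does describe the scheme, and its words, with 10 per condition, point to one place per condition. If blocks were in fact 16, the figures would roughly halve for certainty and the mechanism would remain.

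**Enrolment and delivery are separate.** Site employees deliver the sessions, while the principal investigator or research team screens and consents. A reader might infer that one small team does everything; the article contradicts that. What stands is the narrower link through weekly supervision. It makes past assignments knowable to the enrolling side, but does not show that every recruiter keeps a tally.

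**Participants come forward themselves.** Recruitment is by flyers and a weekly staff presence, and the eligibility criteria leave little discretion. A reader might infer that staff pick clients for particular conditions. The article does not show this. The remaining room is over in-person contact and the timing of enrolment.

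**This is a pilot.** Component effects are exploratory and are to be read as patterns rather than tested. That limits the consequence. But those patterns, with adherence by component, will inform the later optimization trial, and the remedy is cheap.

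**Conclusion.** The point holds in a limited form. On the natural reading of the Randomization section, the end of each block is predictable to enrolling staff who follow past assignments: about 10 of 80 allocations for the exact condition and about 16 of 80 for a given component. The best-guess rates of 34% and 66.6% are upper limits.

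This rests on two assumptions: block size 8, which is inferred, and knowledge of past assignments and block starts, which the described roles make possible but do not prove.

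Two stronger readings should be resisted. Staff cannot work out upcoming allocations in general, because the exact condition is certain only at the last place in a block. Nor do the documents show that selection has occurred or that the contrasts are biased. It is an avoidable weakness in the stated scheme that should be corrected while allocations remain.

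**What to change.** 1. For the allocations not yet used, load a new REDCap allocation table of permuted blocks of 8 and 16 in random order, generated by someone with no part in enrolment.
2. Constrain the block sizes to sum to the places that remain. Unconstrained draws can overshoot 80 and break the 10 per condition. If the change falls inside a block, finish that block first, so that the remainder is a multiple of 8.
3. Replace the parenthesis in Randomization with wording such as: assignments are made in permuted blocks of randomly varying size; the sizes and the sequence are withheld from staff who recruit, screen or obtain consent.

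The cost is one new table and a sentence of protocol text. Sample size, power and conditions do not change. Balance may be slightly looser if enrolment stops early. Recruitment began in December 2024 and the number of unused places is not given, so the benefit shrinks the longer the change waits. Some predictability remains whatever multiple of 8 is used.

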### Intervention

The intervention period for each participant will last from 1 to 5 weeks, depending on the experimental condition. The conditions have a maximum of 5 sessions, delivered once per week, and sessions last for up to 1.5 hours (refer to content in Table 2). Following a baseline assessment, the core intervention will be delivered for all participants, and additional components will be delivered subsequently in the following weeks. In addition, participants are expected to attend all appointments for mental health treatment at the study site. All intervention components will be delivered by a mental health clinician and a professional peer specialist employed by the study site. The principal investigator will provide initial and ongoing training to the interventionists on the manualized intervention components and reporting procedures for adverse events throughout the study.

**Table 2 table2:** Content and duration of components.

Component	Number and duration of sessions	Topics and activities
Just Do You	1 Session 60 minutes	Guiding principles of recovery Recovery Role Model personal narrative Videos of celebrity service users Personal goals related to recovery Characteristics of a trustworthy professional Introduction to clinic services
A: Cultural identity	1 Session 60 minutes	Feeling seen and heard Introduction to creative arts therapy techniques Cultural identity art activity Recovery Role Model personal narrative
B: Future self	2 Sessions 60 & 30 minutes	Session 1 Overcoming challenges and finding hope Introduction to creative arts therapy techniques Mental health resilience in music and videos Strengths and inspiration of art activity Recovery Role Model personal narrative Introduce guidelines for photo activity Session 2 Brief check-in after completing the photo activity
C: Understanding environments	1 Session 60 minutes	Overcoming barriers in the environment Introduction to creative arts therapy techniques Map of your environment art activity Recovery Role Model introduces services/strategies for addressing barriers to engagement

### Assessment Procedures

Assessments of engagement will occur at baseline, posttest (after intervention completion), and 3-month follow-up. At each assessment, participants will report on involvement in their treatment, and their perceptions of stigma, benefits, trust and rapport with providers, hopefulness, and the difficulty associated with treatment engagement. In-depth acceptability interviews will be conducted at posttest with 40 participants purposively sampled from each experimental condition. Acceptability interviews will be focused on experiences with intervention components, aspects of implementation, and any factors that promoted or impeded intervention adherence. Each assessment is expected to last for 1 hour.

Screening, consent, and assessment interviews with participants will be administered by the principal investigator or another trained member of the research team and will take place in person at the study site or via encrypted videoconferencing. All staff involved in data collection will be trained on the assessments by the principal investigator, and all research staff will complete training on informed consent, good clinical practices, and all safety and reporting protocols as certified by New York University’s institutional review board (IRB).

#### Process Evaluation

To determine the extent to which the program is delivered as intended, treatment fidelity will be monitored by research staff who observe selected sessions and rate the content delivered using checklists. Interventionists will use session checklists to record the content delivered and attendance in each session, and report on issues that arise regarding participants and study activities. The principal investigator will hold weekly supervisory meetings with interventionists to review the study process, receive feedback, and see that concerns are addressed in a timely manner.

#### Measures

Acceptability will be measured by a self-report questionnaire based on the theoretical framework of acceptability [82]. The scale has 9 items (eg, how much effort did it take you to participate in the intervention sessions?), with total scores ranging from 9 to 45, and higher scores indicating greater acceptability. Can be found in Multimedia Appendix 1 for interview guide. We will also record rates of intervention adherence as the number of assigned components completed by participants. To assess feasibility, we will record rates of recruitment, enrollment, retention, and assessment, and attempt to learn reasons for any dropouts through follow-up contacts. We will document interventionists’ feedback throughout the study to determine component challenges and facilitators, and any key aspects they believe are of particular importance to the intervention. We will also regularly meet with administrative staff from the study site to assess their perceptions of the study’s impact (challenges/benefits) on the clinic and document their ideas for overcoming any challenges to implementation. These meetings will clarify the elements involved in the feasible implementation of the intervention and the overall study, such as the integration of the study into the clinic workflow.

Engagement in treatment will be measured using 8 items from the Client Engagement in Child Protective Services Scale involvement or buy-in subscale [83]. Responses are on a 5-point Likert scale. An example item is “I am not just going through the motions. I’m really involved in working with providers.” The range for the scale is 8 to 40, with higher scores indicating higher levels of engagement. This scale has demonstrated acceptable reliability with the study target population (=.82) [51,83]. Service usage will be measured at a 3-month follow-up by participant medical records. The total number of contacts each participant makes with the treatment program, and the dates for all contacts, starting 1 month before baseline through 3-month follow-up, will be collected to assess change in service use over the study period. Demographic information will be collected at baseline, and targeted mediators and mental health symptoms will be collected by self-report measures at all timepoints. Study measures have been extensively tested by the research team [84] and previous studies with REM populations, young adults, and individuals living with SMI. All have been found to have good psychometric properties. Can be found in Multimedia Appendix 2: Baseline assessment measures for a full list of the study measures collected during the baseline assessment.

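### The service-use count is defined as all program contacts and does not exclude the assigned study sessions, so if those are charted it would favor each component by up to 1 (A), 2 (B) or 1 (C) contacts

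*Protocol article*

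**What the plan says.** All references are to the Methods of the protocol article.

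- **Measures** gives the source: "Service usage will be measured at a 3-month follow-up by participant medical records". It defines the quantity as "The total number of contacts each participant makes with the treatment program, and the dates for all contacts", and gives the period as "starting 1 month before baseline through 3-month follow-up, will be collected to assess change in service use over the study period".
- **Study Timeline** describes the extract as a "report from the study site documenting each date a treatment service was received by the participant over the study period".
- **Intervention** says who runs the sessions: "All intervention components will be delivered by a mental health clinician and a professional peer specialist employed by the study site". It then adds: "In addition, participants are expected to attend all appointments for mental health treatment at the study site".
- **Table 2** lists one session for the core, one for A, two for B and one for C. Sessions are weekly, with at most five per participant.
- **Process Evaluation** has the interventionists log attendance at each session on checklists.
- **Data Analysis** fits an effect-coded factorial ANOVA to the change in service contacts. It says interpretation will rest on the pattern of results, including strength and direction, and not on hypothesis tests.

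**The concern.** The outcome is meant to show whether a component leads participants to use more of the clinic's services. The component is itself one or two meetings with clinic staff, held inside the counting window. If those meetings enter the count, part of the outcome is simply the assigned exposure.

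Randomization and intent-to-treat analysis do not remove this, because assignment creates the difference. Taking change from the pre-baseline month does not remove it either, because no study session falls in that month.

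Every component would be pushed in the favorable direction, and B twice as far as A or C because it has two sessions. Size and direction are what the exploratory analysis intends to read. The Discussion says that understanding the relative value of the components is likely to inform improvements to the intervention.

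**Working it through.** **The plan's own figure.** The article gives no expected mean or SD for contacts. The nearest stated figure is 79% power for d = 0.50, with correlation 0.6, N = 80 and α = .05. With 40 participants per factor level and a baseline-adjusted SD of √(1 − 0.6²) = 0.8, the noncentrality is (0.50/0.8) × √(40/2) = 2.795. Two-sided power is 79.8% by the normal approximation and 78.8% by the t distribution with 78 df, so 79% reproduces. It neither supports nor refutes this point. It only supplies d = 0.50 as a yardstick.

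**Inputs.** Sessions (Table 2): core 1, A 1, B 2, C 1. Conditions and contrast (Table 1, Pilot Trial Design): eight cells of 10, so each main effect compares 40 included with 40 excluded. Completion benchmark (Data Analysis): 85%.

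**Step 1: contacts added per cell if every session is attended and charted.** Added contacts = 1 + A + 2B + C, with each factor 0 or 1.

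| Condition | 1 | 2 | 3 | 4 | 5 | 6 | 7 | 8 |
|---|---|---|---|---|---|---|---|---|
| Added contacts | 1 | 2 | 3 | 4 | 2 | 3 | 4 | 5 |

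**Step 2: included minus excluded, with no true effect.**

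- A: (2+3+4+5)/4 − (1+2+3+4)/4 = 3.5 − 2.5 = **+1**
- B: (3+4+4+5)/4 − (1+2+2+3)/4 = 4 − 2 = **+2**
- C: (2+4+3+5)/4 − (1+3+2+4)/4 = 3.5 − 2.5 = **+1**

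The effect-coded coefficients are half of these (0.5, 1.0, 0.5). All interactions are 0, and the core session cancels because everyone receives it.

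**Step 3: incomplete attendance.** The shift scales with attendance. Reading the 85% benchmark as session attendance (an assumption), it is 0.85 × (1, 2, 1) = 0.85, 1.70, 0.85.

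**Step 4: sessions not charted as contacts.** The shift is 0, 0, 0.

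**Step 5: standardized size at full attendance.** d = shift/SD, over an assumed range of SD.

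| Assumed SD of contacts | A or C (shift 1) | B (shift 2) |
|---|---|---|
| 4 | 0.25 | 0.50 |
| 8 | 0.125 | 0.25 |
| 12 | 0.08 | 0.17 |

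**The case against.** The strongest reply is that the article treats study sessions and clinic services as different things. The sentence on treatment appointments in Intervention begins by naming them as additional to the sessions. Study Timeline asks the site for dates on which a *treatment service* was received, and Data Analysis also speaks of treatment services. Session attendance has its own log and its own measure, intervention adherence. On that reading the sessions never enter the count. It can also be said that which record entries qualify is a derivation detail for a fuller document, and that the trial is a pilot that disclaims hypothesis testing.

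Much of this stands. A reader might infer that the components certainly raise the outcome by 1, 2 and 1 contacts. The document does not support that. It never says study sessions are charted as contacts. It gives the employer of the people delivering the sessions, not how a session is recorded. The figures are also maxima: missed sessions reduce them, and if the count is of distinct dates, a session on a day when another service is received adds nothing. A reader might also go on to quote false-positive rates, but those would describe a testing rule that the analysis section sets aside.

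What does not stand is the conclusion that nothing needs changing. None of those sentences is an exclusion rule. The one place that defines the measure is all-inclusive as to both contacts and dates, so this is more than an unstated detail: the stated definition, followed as written, takes in the assigned sessions. Dropping significance tests gives no protection when the strength and direction of effects are what will be read.

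**Conclusion.** The point holds conditionally and is of moderate importance. The definition of service use covers all program contacts in a window that contains the assigned sessions, and the remaining text leaves it unclear whether those sessions count.

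If they do, the main effects on contacts are inflated by up to +1 (A), +2 (B) and +1 (C), and by 0.85, 1.70 and 0.85 at 85% attendance. If they are not charted as contacts, there is no inflation. In standardized terms the maximum is about 0.50 to 0.17 for B and 0.25 to 0.08 for A or C, on an assumed SD of 4 to 12. At the low end of that range, B's artifact alone equals the d = 0.50 used in the power statement.

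Only the contact count is at risk; the self-reported engagement scale does not depend on it.

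**What to change.** Define the service-use outcome as contacts for usual clinic services, excluding every Just Do You and component A, B and C session. Identify those sessions by matching the interventionists' checklists to the dated contacts from the site. Bring the wording in Measures, Study Timeline and Data Analysis into line with this definition, and fix the rule before outcomes are analyzed.

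Add a sensitivity count over a post-intervention window common to all conditions, for example week 6 after baseline through month 3. With at most five weekly sessions starting within a week of baseline, no condition should have study sessions left by then. Any session that slips past week 5 would still be removed by the checklist match. This window also avoids other services picked up on the day of a session.

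The cost is a few hours of date matching and a sentence in the outcome definition. No new data are needed, since contact dates and session attendance are already collected. The downside is that the sensitivity count covers a shorter period.
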